## Abstract

**Background:**

Tumor-informed circulating tumor DNA (ctDNA) analysis allows for the sensitive detection of minimal residual disease (MRD) and has the potential to enhance patient stratification for adjuvant chemotherapy. We hypothesize that intensifying adjuvant chemotherapy in colon cancer patients with postoperative MRD positivity may reduce recurrence and improve survival outcomes.

**Methods:**

This multi-center platform trial (NCT05534087) consists of a prospective observational study (Part 1) and an interventional randomized trial (Part 2). In Part 1, approximately 1,200 patients with colon cancer will be screened for MRD at 3–6 weeks postoperatively using a tumor-informed, hybrid-capture-based ctDNA MRD assay that tracks up to 100 patient-specific somatic variants identified through tumor whole-exome sequencing.

Key eligibility criteria includes: age ≥ 19 years, ≤ 6 weeks post-curative resection, pathological diagnosis of colon adenocarcinoma, stage III or stage II with high-risk features requiring adjuvant chemotherapy with FOLFOX/CAPOX, and no macroscopic residual disease. All patients in Part 1 will complete 3 months of standard adjuvant FOLFOX/CAPOX while awaiting MRD results. Patients with MRD positivity will be screened for the Part 2 clinical trial following the completion of the initial 3 months of treatment titled “*Randomized Controlled Phase III Trial of Treatment Intensification in Stage II–III Colon Cancer Patients with Positive MRD after Curative Resection.*” MRD-negative patients are managed at the investigator’s discretion.

Part 2 investigates the superiority of an experimental arm (modified FOLFIRINOX for 3 months) compared to a control arm (FOLFOX/CAPOX for 3 months). The primary endpoint of the Part 2 randomized trial is the 3-year disease-free survival (DFS), while secondary endpoints include the 5-year overall survival, 5-year DFS, treatment-related adverse events, treatment compliance, and patient-reported outcomes. A total of 236 patients will be enrolled and randomized in a 1:1 ratio, assuming a hazard ratio of 0.64, 80% power, a two-sided alpha of 0.05, and a 10% dropout rate.

**Discussion:**

This trial will evaluate the effect of adjuvant chemotherapy intensification in colon cancer patients who are MRD-positive after curative surgery. This will enable a personalized adjuvant chemotherapy strategy based on postoperative MRD assessment in colon cancer.

**Trial registration:**

ClinicalTrials.gov: NCT05534087.

Clinical Research Information Service: KCT0007644.

## Background

The standard treatment for patients with high-risk stage II and stage III colon cancer consists of curative surgery followed by adjuvant chemotherapy with fluoropyrimidines and oxaliplatin [1, 2]. Although most patients are treated based on pathological stage and clinicopathological risk factors for recurrence, it is estimated that approximately half of patients with stage III colon cancer are cured by surgery alone, while only about one-quarter truly benefit from adjuvant chemotherapy [3, 4].

Recent studies across various solid tumors have demonstrated that circulating tumor DNA (ctDNA) analysis can detect minimal residual disease (MRD) even in the absence of radiographic or clinical evidence of disease, thereby substantially improving the prediction of recurrence [5–10]. Among patients with stage III colon cancer who receive standard adjuvant chemotherapy (FOLFOX or CAPOX) after curative resection, the 3-year disease-free survival (DFS) rate is approximately 75% [11, 12]. However, although research on ctDNA-guided MRD in colon cancer is still emerging, recent studies suggest that postoperative MRD-positive patients with stage II-III disease may have a 3-year DFS of around 30% even after standard adjuvant therapy and could account for more than half of all relapses among treated patient [5–7, 10]. Despite this high-risk profile, the current standard of care for MRD-positive patients remains 3–6 months of FOLFOX or CAPOX, regardless of MRD status [1, 2].

In this context, we designed a prospective, multi-center platform study (CLAUDIA Colon Cancer, KCSG CO22-12) to better characterize clinical outcomes in colon cancer patients according to their postoperative MRD status and to evaluate the clinical utility of MRD-informed treatment decisions in a controlled trial setting. The study comprises two parts: a prospective observational cohort (Part 1) and an interventional randomized clinical trial (Part 2). The platform design was adopted to allow for the future integration of additional MRD-guided interventional trials, reflecting the growing potential of MRD-based strategies in colorectal cancer management [13].

Currently, within Part 2, we are conducting a randomized controlled trial testing the hypothesis that incorporating a 3-month course of intensified treatment with modified FOLFIRINOX (mFOLFIRINOX) following an initial 3 months of standard FOLFOX or CAPOX may significantly improve 3-year DFS in MRD-positive patients with stage II–III colon cancer after curative resection.

## Methods

### Study aim and design

This multi-center, prospective, open-label, platform trial consists of two sequential parts: a prospective observational study (Part 1) and a randomized controlled phase III clinical trial (Part 2) (Fig. 1). Part 1 involves screening approximately 1,200 patients for MRD using postoperative ctDNA analysis, while Part 2 evaluates the efficacy of intensified chemotherapy (3 months of FOLFOX or CAPOX followed by 3 months of mFOLFIRINOX) versus standard chemotherapy (6 months of FOLFOX or CAPOX) in MRD-positive patients identified in Part 1 (Fig. 2).

**Fig. 1 Fig1:**
[figure not shown]
Overall study schema illustrating Part 1 and Part 2 of the study. Abbreviations: MRD, minimal residual disease; CEA, carcinoembryonic antigen; ctDNA, circulating tumor DNA

**Fig. 2 Fig2:**
[figure not shown]
Detailed schematic of the Part 2 study design. Abbreviations: MRD, minimal residual disease; CEA, carcinoembryonic antigen; ctDNA, circulating tumor DNA

### Participants

Eligible patients for Part 1 observational study are adults aged ≥ 19 years with histologically confirmed stage III or high-risk stage II colon adenocarcinoma who underwent curative surgical resection (R0) within the past 6 weeks and plan to receive standard adjuvant chemotherapy (FOLFOX or CAPOX). For stage II colon cancer, high-risk was defined as having ≥ 1 risk factor: pathological T4; poorly differentiated/undifferentiated histology; lymphatic/vascular invasion; perineural invasion; < 12 lymph nodes examined; bowel obstruction; localized perforation; close, indeterminate, positive margins; or tumor budding. Additional eligibility criteria include no macroscopic metastatic or residual disease on both abdomen-pelvis and chest CT taken within 4 weeks before or after surgery, adequate organ function, ECOG performance status 0–1 (0 for ≥ 70 years), and no prior chemotherapy or radiotherapy for colon cancer. Detailed eligibility criteria are listed in Table 1.

**Table 1 Tab1:** Detailed patient eligibility criteria for part 1 and 2 studies

Inclusion criteria	Exclusion criteria
1. Written informed consent 2. Age ≥ 19 years 3. ECOG performance status 0–1 (ECOG 0 required if age ≥ 70) 4. Histologically confirmed adenocarcinoma of the colon (including rectosigmoid colon above the peritoneal reflection) 5. Pathological stage II–III colon cancer with high-risk features, including one or more of the following: • T4 lesion • Poor differentiation • Lymphatic or vascular invasion • Bowel obstruction • Fewer than 12 lymph nodes examined • Perineural invasion • Tumor perforation • Positive resection margins • Tumor budding 6. No evidence of distant metastasis on imaging (contrast-enhanced CT of the abdomen/pelvis and chest) performed within 4 weeks before or after surgery 7. apable and willing to comply with study procedures until study completion **Part 1–Specific Criteria:** 8. Planned initiation of adjuvant chemotherapy with FOLFOX or CAPOX within 6 weeks after curative (R0) resection 9. Agreement to participate in Part 2 if postoperative ctDNA testing indicates MRD positivity **Part 2–Specific Criteria:** 10. Completion of 6 cycles of FOLFOX or 4 cycles of CAPOX as adjuvant chemotherapy following R0 resection 11. Confirmed minimal residual disease (MRD) based on ctDNA testing performed 3–6 weeks postoperatively 12. Adequate bone marrow function: • ANC ≥ 1,300/µL • Platelets ≥ 75,000/µL • Hemoglobin ≥ 8.0 g/dL (patients requiring intermittent transfusions may still be eligible) 13. Adequate hepatic function: • Total bilirubin ≤ 1.5 × ULN • AST and ALT ≤ 3 × ULN 14. Adequate renal function: • Serum creatinine ≤ 1.5 × ULN • Creatinine clearance ≥ 50 mL/min	1. Refusal to participate in, or medical unsuitability for, the Part 2 trial (mFOLFIRINOX therapy) 2. Non-adenocarcinoma histology 3. Planned adjuvant chemotherapy that does not include oxaliplatin 4. Prior chemotherapy or radiotherapy before or after curative resection 5. History of other malignancies within the past 3 years, except for completely treated basal cell carcinoma of the skin, carcinoma in situ of the cervix, or thyroid cancer 6. Incomplete resection (R1 or R2 resection) 7. Evidence of recurrence or residual tumor on imaging or clinical examination 8. Diagnosis of familial adenomatous polyposis (FAP) or other polyposis syndromes 9. Diagnosis of two or more synchronous colon cancers of clinical or pathological stage II or higher, either concurrently or within the past 3 years 10. Pregnancy or lactation 11. Uncontrolled serious infections or other uncontrolled comorbidities 12. Significant or unstable pre-existing medical or psychiatric conditions that, in the opinion of the investigator, may compromise patient safety during the study **Part 2–Specific Criteria:** 13. Sexually active males and females of childbearing potential who are unwilling to use effective contraception during the treatment period and for 6 months after the last dose 14. Clinically significant cardiovascular disease, including: • Unstable angina requiring treatment • Symptomatic coronary artery disease • Congestive heart failure (NYHA class II or higher) • Serious cardiac arrhythmias • Acute coronary syndrome (e.g., myocardial infarction) within the past 6 months 15. Active viral infections such as HIV (Note: hepatitis B carriers may be eligible at the investigator’s discretion, with prophylactic antiviral therapy permitted) 16. Symptomatic inflammatory bowel disease 17. History of allogeneic transplantation requiring immunosuppressive therapy 18. Participation in another clinical trial involving investigational drugs or devices after curative resection for colon cancer 19. Presence of grade ≥ 3 peripheral neuropathy according to CTCAE v5.0 20. History of severe unexpected adverse reactions to fluoropyrimidines or platinum agents (Patients with anticipated but manageable reactions may be eligible at the investigator’s discretion) 21. Known Gilbert’s syndrome, dihydropyrimidine dehydrogenase (DPD) deficiency, or homozygosity for UGT1A1*28 alleles

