
### Procedures and interventions

In Part 1, patients undergo ctDNA MRD testing (CancerDetect™, IMBdx Inc.) using 20 mL whole-blood sample collected 3–6 weeks after surgery [10, 14–16]. Whole-exome sequencing (WES) of the surgical tumor tissue and matched white blood cells is first performed to identify patient-specific somatic mutations. Based on these findings, a personalized target capture panel comprising up to 100 variants is designed. ctDNA MRD testing is then conducted by high-depth sequencing of postoperative plasma DNA using this customized panel.

All enrolled patients initially receive 3 months of standard chemotherapy (FOLFOX/CAPOX). MRD test results will be disclosed to investigators and study participants within 3 months of initiating chemotherapy. For MRD-negative patients identified after completing the initial 3 months of standard chemotherapy, the decision to continue with an additional 3 months of chemotherapy (to complete a 6-month course) or to stop after 3 months will be left to the investigator’s discretion. MRD-positive patients will be screened for participation in Part 2 of the study after completion of the 3 months of chemotherapy. A total of 236 MRD-positive patients will be randomized 1:1 to receive either intensified chemotherapy (3 months of mFOLFIRINOX) or continued standard chemotherapy (an additional 3 months of FOLFOX or CAPOX).

The mFOLFIRINOX regimen consists of oxaliplatin (85 mg/m^2^), leucovorin (400 mg/m^2^), irinotecan (150 mg/m^2^), and 5-fluorouracil (2,400 mg/m^2^ for 46 h as a continuous infusion). The first dose of the clinical trial treatment is recommended to be administered on the scheduled start date of the next cycle of adjuvant chemotherapy—cycle 7 for FOLFOX or cycle 5 for CAPOX—and must be given within 3 weeks following randomization. Administration within + 7 days from Day 1 of each treatment cycle is permitted.

Stratified randomization was employed using mixed block sizes of 2 and 4 within each stratum. Patients are assigned through the web-based clinical trial platform system called Mytrial. The stratification factors were:•Risk group: high-risk (stage III colon cancer with T4 and/or N2) vs. low-risk (stage III without T4/N2 or stage II colon cancer)•Adjuvant chemotherapy regimen: FOLFOX vs. CAPOX•Study site

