### Statistical analysis

A total sample size of 236 patients (118 per arm) of the Part 2 study was calculated based on an assumed hazard ratio (HR) of 0.64 for 3-year DFS, providing 80% power with a two-sided alpha of 0.05, and accounting for a 10% dropout rate. This HR corresponds to an estimated 3-year DFS rate of 46.3% in the experimental arm and 30.0% in the control arm, reflecting a clinically meaningful and statistically significant absolute improvement of 16%.

Assuming uniform accrual over 3 years and a minimum follow-up of 3 years for the last enrolled patient, a total of 159 DFS events is required. One interim efficacy analysis is planned after 30% of events have occurred. Sample size estimation was performed using the rpact package in R (version 4.1.1).

Survival outcomes (DFS and OS) will be analyzed using the Kaplan–Meier method and compared between treatment groups using the stratified log-rank test, with stratification factors identical to those used at randomization. Treatment effects will be estimated using a stratified Cox proportional hazards model to calculate the HR and its corresponding two-sided 95% confidence interval (CI).

Efficacy analyses for Part 2 will be performed primarily using the Full Analysis Set (FAS), defined as a modified intention-to-treat (mITT) population that includes all randomized patients who have received at least one dose of the investigational product, in accordance with the ITT principle. Patients will be excluded from the FAS if they (1) do not meet key eligibility criteria, (2) have not received any investigational product, or (3) have not undergone at least one post-randomization assessment.

Sensitivity analyses will be conducted on the Per Protocol Set, a subset of the FAS that includes patients who adhere to the protocol. Safety analyses will be based on the Safety Set, defined as all patients who received at least one dose of the investigational product.

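### Table 1 conflicts with the main text on stage III and with itself on margins and prior chemotherapy, while failing undefined key eligibility criteria removes randomized patients from the primary analysis

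*Protocol article*

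**What the plan says.** **Stage.** The abstract (Methods) admits "stage III or stage II with high-risk features requiring adjuvant chemotherapy with FOLFOX/CAPOX". The Participants section admits patients with "histologically confirmed stage III or high-risk stage II colon adenocarcinoma who underwent curative surgical resection (R0) within the past 6 weeks" and limits the scope of the risk list: "For stage II colon cancer, high-risk was defined as having ≥ 1 risk factor". Table 1, inclusion 5, reads "Pathological stage II–III colon cancer with high-risk features, including one or more of the following". Its list has T4, differentiation, lymphatic or vascular and perineural invasion, obstruction, node count, perforation, margins and budding. Nodal category is not on it.

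**Margins.** Positive margins are a qualifying feature both in the Participants text and in Table 1, inclusion 5. The Participants text and Table 1, inclusions 8 and 10, require R0 resection, and exclusion 6 removes "Incomplete resection (R1 or R2 resection".

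**Earlier chemotherapy.** Exclusion 4 bars "Prior chemotherapy or radiotherapy before or after curative resection". It stands above the Part 2 heading of the exclusion list, so it belongs to the criteria common to both parts. Part 2 inclusion 10 requires six cycles of FOLFOX or four of CAPOX after R0 resection.

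**Analysis set.** The Statistical analysis section makes the Full Analysis Set (FAS), a modified intention-to-treat population, the primary efficacy set. It presents that set as consistent with the intention-to-treat principle, yet excludes randomized patients who "do not meet key eligibility criteria". The section does not say which criteria are key. Study aim and design describes the trial as open-label.

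**The concern.** Eligibility text that contradicts itself would normally be a drafting matter. Here it also feeds a rule that decides who is counted for the primary endpoint. If a stage III patient without a listed feature is randomized, one wording keeps that patient in the FAS and the other makes the patient an eligibility failure. The choice is made after randomization, in a trial where treatment is known, and the article does not say that it is made blind to arm and outcome. At stake are the comparability that randomization provides and, to a lesser extent, the number of events available to the primary test.

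**Working it through.** The check is mainly a comparison of text, followed by an illustration of size.

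**1. Stage.** Take a T3N2 patient with none of the listed features.

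| Source | Result |
|---|---|
| Abstract, Methods | Eligible: any stage III |
| Participants text | Eligible: any stage III; the list applies to stage II |
| Table 1, inclusion 5 | Not eligible: no listed feature, and N2 is not listed |
| Procedures and interventions, stratification | High-risk stratum: stage III with T4 and/or N2 |

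The same conflict affects any stage III patient without a listed feature. The Participants section refers to Table 1 for the detailed criteria, so the table cannot be set aside as the looser version.

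**2. Margins.** A patient who qualifies only by a positive margin meets inclusion 5 but not the R0 requirement, and meets exclusion 6. The Participants text has the same internal conflict, so this is not Table 1 against the rest of the plan. Exclusion 6 settles the outcome, so the practical effect is small.

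**3. Earlier chemotherapy.** Exclusion 4 has no time point. Applied again at Part 2 entry, it cannot be satisfied together with inclusion 10. Applied at Part 1 entry only, there is no conflict.

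**4. Link to the analysis.** The only list that the article labels as key eligibility criteria is in the abstract. It includes stage and curative resection, so two of the three disputed topics can plausibly count as key.

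**5. Size.** The article gives no rate of eligibility failure, so no corrected figure follows. First, the plan's own event number (Statistical analysis: HR 0.64, two-sided alpha 0.05, power 80%, 1:1 allocation), by Schoenfeld's formula:

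- d = 4(1.960 + 0.842)² / (ln 0.64)² = 157.6, rounded up to 158, against 159 stated. This reproduces to within one event.
- Power at d events = Φ(|ln 0.64|·√d / 2 − 1.960). At d = 159 it is 80.3%.

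Now assume that a share x of the 159 events leaves the FAS and is not replaced. The range for x is an assumption.

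| x | Events left | Power at HR 0.64 |
|---|---|---|
| 2% | 156 | 79.5% |
| 5% | 151 | 78.3% |
| 10% | 143 | 76.1% |
| 20% | 127 | 71.1% |

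This shows loss of information only. Bias from selective removal cannot be computed from the article.

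**The case against.** The strongest case for the plan is that these are compressed table entries whose intended meaning is visible elsewhere. The Participants text states that the list serves stage II, and the abstract's key-criteria list carries the same stage wording. Exclusion 4 sits beside items that make sense only at Part 1 entry, such as a planned regimen without oxaliplatin, and the Participants text gives the ban on earlier chemotherapy among the Part 1 criteria. The key criteria and their adjudication may be defined in the SAP, and stage, margins and treatment before entry are all fixed before randomization.

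Much of this stands, and it limits the point. Three stronger readings are tempting and are not supported:

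- A reader might infer that every Part 2 patient meets an exclusion criterion. That follows only if exclusion 4 is applied afresh at Part 2 entry. The Discussion reports 116 patients already enrolled in Part 2, so the literal reading is not in use.
- A reader might take the stratum "low-risk (stage III without T4/N2 or stage II colon cancer" as proof against inclusion 5. It is not: a stage III patient without T4 or N2 can have another listed feature. The stage conflict rests on the abstract and the Participants text.
- A reader might infer that sites are enrolling different populations. The article condenses a full protocol that is not shown, and nothing in it reports this.

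What the objection does not remove is that the operative wording differs on stage III, and that the article itself states the rule taking eligibility failures out of the primary set. A definition of key criteria in the SAP would narrow that rule, but patients would still be removed after randomization.

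**Conclusion.** The point holds as an inconsistency in operative eligibility rules with a consequence for the primary analysis. The stage III conflict is the substantive one. The margin conflict is nearly inert because exclusion 6 governs. The conflict over earlier chemotherapy is probably a missing time point. Together they make membership of the FAS depend on which wording is applied, in an open-label trial whose primary set is presented as following intention-to-treat.

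The number of patients affected is not given and may be small, since the intended reading can be guessed. The power figures rest on assumed loss rates and on an unchanged hazard ratio. The article does not show that any patient has been removed on these grounds, or that such a decision would be taken with outcomes in view; it shows only that the rule as stated leaves room for it. The matter should be corrected, but it does not invalidate the design.

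**What to change.** 1. Reconcile the stage wording of Table 1, inclusion 5, with the abstract and the Participants text, and reconcile the margin item with the R0 requirement and exclusion 6, so that one version governs throughout. Which clinical criterion should apply is for the sponsor to decide.
2. State the time point at which exclusion 4 applies, so that it can be read together with Part 2 inclusion 10.
3. Make the primary efficacy analysis include all randomized patients in the arm to which they were assigned, and keep the eligibility-restricted set as a sensitivity analysis. At minimum, name the key criteria, restrict them to facts fixed from pre-randomization data, and have them judged blind to arm and outcome.

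The cost is a wording amendment and a change to the definition of the analysis set. No new data are needed beyond continued follow-up of every randomized patient, and the target of 236 patients does not change. The amendment should be made before DFS is examined by arm, and so before the interim analysis planned at 48 events; a later change would be open to challenge.
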